#### Aim 2: Candidate Gut-Brain Mechanisms

We hypothesize that participation in WISH 2.0 will be associated with changes in at least one of the following candidate gut-brain mechanisms: autonomic function (heart rate variability [HRV]), interoception (self-report measure), stress-related gene expression (whole transcriptome RNA sequencing), and immune system activation (serum inflammatory biomarkers). We further hypothesize that any changes in these candidate mechanisms will be associated with reductions in IBS symptom severity over time.

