#### Exploratory Clinical Outcomes

The comparative effects of the interventions on several health-related, psychological, and health behavior outcomes will be explored at baseline, intervention midpoint, immediately after the intervention, and 3 months after the intervention (ie, extended follow-up). Health-related outcomes include IBS symptom severity (IBS-SSS; primary exploratory clinical outcome) [52], health-related quality of life (IBS Quality of Life Instrument [IBS-QOL] [73]), and IBS diagnosis (Rome IV Diagnostic Questionnaire—IBS Module) [51]. Consistent with the literature [52,74], the MCID for within-participant change from baseline for this trial will be defined a priori as a reduction of ≥50 points in the IBS-SSS total score at the postintervention assessment. Psychological outcomes include positive affect (Positive and Negative Affect Schedule [PANAS] [75]), optimism (Life Orientation Test-Revised [LOT-R] [76] and the Brief State Optimism Measure [B-SOM] [77]), resilience (Brief Resilience Scale [BRS] [78]), self-efficacy (General Self-Efficacy Scale [GSE] [79]), depression and anxiety (Hospital Anxiety and Depression Scale [HADS] [80]), GI symptom-specific anxiety (Visceral Sensitivity Index [VSI] [81]), response to pain (the Pain Catastrophizing Scale [PCS] [66]), and perceived stress (the Perceived Stress Scale (PSS) [82]). Health behavior outcomes include physical activity (International Physical Activity Questionnaire [IPAQ] [83]) and avoidant and restrictive eating (Nine Item Avoidant/Restrictive Food Intake Disorder Screen (NIAS) [84]).

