#### Exploratory Mechanistic Outcomes

Exploratory mechanistic outcomes include autonomic function (as measured by HRV frequency-domain variable measures, specifically low-frequency power, high-frequency power, and the low-frequency/high-frequency ratio [85,86], using the HeartMath Institute emWave Pro Plus), self-reported interoception (Multidimensional Assessment of Interoceptive Awareness Version 2 [MAIA-2] [87]), stress-mediated gene expression (whole transcriptome analysis of blood by RNA sequencing), and immune system activation (serum inflammatory biomarker levels, such as interleukin-6, tumor necrosis factor-α, and C-reactive protein). Each of these 4 candidate gut-brain mechanisms is known to contribute to IBS pathophysiology (at least in subsets of patients) [88-99] and has established associations with PP well-being [100-104]; thus, each holds promise as a potential mechanism linking PP well-being and IBS symptom severity. These exploratory mechanisms will largely be assessed before and immediately after the intervention, except for interoception, as this is measured by a questionnaire that can be completed remotely at the intervention midpoint and extended follow-up.

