#### Statistical Analysis Plan

Feasibility will be assessed using proportions and exact binomial CIs. Acceptability will be evaluated using a random-effects model with a participant-specific random effect to account for within-participant correlation among ratings. This model will also facilitate estimation of the between- and within-participant variance of the ratings. Qualitative exit interviews will be coded by 2 independent coders with a goal of interrater reliability >0.80. Discrepancies will be resolved by consensus, and themes will be derived from iterative review of coded data. To assess the immediate impact of the respective exercises on happiness, optimism, and IBS knowledge, 2-tailed paired *t* tests will be used. Between-group differences in the proportion who achieve the MCID (≥50-point reduction in the IBS-SSS) will be evaluated using logistic regression. Achieving the MCID (yes or no) will be modeled as the dependent variable, with treatment group (WISH 2.0 vs educational control) included as the primary independent variable. For clinical outcomes that are measured multiple times per participant, preliminary effects will be explored using mixed-effects regression models with fixed effects for a categorical effect of time and a time-by-treatment interaction with a common baseline for the 2 groups, and an unstructured covariance matrix for the residuals to account for repeated measures. The time-by-treatment interaction terms will estimate the difference between groups in the change over time. Because the mixed-effects model uses maximum likelihood to estimate the coefficients, this approach is valid when missing data are missing at random. Effect sizes (modified Cohen *d*) will be calculated by dividing the group×time coefficient by the SD of the difference estimated using the appropriate variance components from the unstructured covariance matrix. Exploratory mechanistic analyses will use linear mixed models to assess changes in candidate gut-brain mechanisms (eg, HRV, interoception, gene expression, and immune activity) in response to the intervention. If there are skewed distributions in the candidate mechanistic data, logarithmic transformations will be applied. Given the exploratory nature of these analyses, no correction for multiple comparisons will be used. In addition to the models that examine each outcome separately, we will also preliminarily explore whether these gut-brain mechanisms might mediate IBS symptom change using a mediation model. We will calculate the change in the candidate mechanism measurements using linear regression for each participant and the change in the clinical effects outcome measures. Then, we will fit a mediation model with the change in the clinical effects outcome measures as the outcome, the change in the mechanistic measurements as the mediator, and the treatment group as the predictor. The direct and indirect effects of the treatment on the clinical effects outcome measures will be estimated from this approach. Finally, the mediation effects will also be estimated by calculating the change in the treatment effect from the linear mixed model used to assess preliminary clinical effects and the treatment effect from a linear mixed model including treatment, time, time-by-treatment interaction, baseline mechanistic data, and change in mechanistic data as the predictors. The change will show the indirect effect through changes in candidate gut-brain mechanisms. All analyses will be conducted using Stata (version 17). Analyses of clinical and candidate mechanistic outcomes will be conducted on the intention-to-treat population (all randomized participants), with sensitivity analyses using the per-protocol population where appropriate.

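### The first mediation model leaves out the baseline mechanism value that the second estimator includes, which costs precision and leaves the mechanism-to-symptom path open to regression-to-the-mean bias

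*Protocol article*

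**What the plan says.** The Statistical Analysis Plan subsection describes two mediation estimators.

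- **First estimator.** The mechanism change is formed per participant: "We will calculate the change in the candidate mechanism measurements using linear regression for each participant". Then "we will fit a mediation model with the change in the clinical effects outcome measures as the outcome", with "the change in the mechanistic measurements as the mediator, and the treatment group as the predictor". Direct and indirect effects are read from this model. No baseline term is named.
- **Second estimator.** The treatment effect from the clinical mixed model is compared with that from a mixed model that has treatment, time, "time-by-treatment interaction, baseline mechanistic data, and change in mechanistic data as the predictors". Here the baseline mechanism value is named.

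Both baselines are available. Of the mechanisms, the article says: "These exploratory mechanisms will largely be assessed before and immediately after the intervention". The clinical outcomes, IBS-SSS among them, "will be explored at baseline, intervention midpoint, immediately after the intervention, and 3 months after the intervention". The Aim 2 hypothesis that the mediation work serves is that "any changes in these candidate mechanisms will be associated with reductions in IBS symptom severity over time".

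**The concern.** Treatment is randomized; mechanism change is not. The regression of symptom change on mechanism change is therefore observational within arms, and baseline status is its most obvious measured confounder. If mechanism and severity are correlated at baseline and both drift back toward their means, their raw changes correlate even when the mechanism does nothing to symptoms. The article itself holds that each mechanism contributes to IBS pathophysiology in at least some patients, so a baseline correlation is plausible on its own premise.

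The raw change score is also a less precise measure of the treatment effect on the mechanism than baseline-adjusted change.

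At stake is the choice of mechanisms to carry into a larger trial, which the Power and Sample Size subsection gives as the use of these analyses. A biased path could promote a mechanism that mediates nothing or understate one that does.

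**Working it through.** **Inputs from the article.** N=50, 1:1 allocation, two-sided 0.05, mediation effect 0.44, mediator SD 1, treatment-mediator correlation 0.4, stated power 81%.

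**Assumed inputs, which the article does not give.** Pre-post correlation rho (0.3 to 0.9, taken equal for mechanism and symptoms) and baseline mechanism-severity correlation r (0.2 to 0.5 in size). Variables have unit variance.

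**1. The stated power reproduces.** With residual SD 1, power = Phi(0.44 × sqrt(50 × (1 - 0.4²)) - 1.96) = Phi(2.85 - 1.96) = Phi(0.89) = 0.814. No stated figure is wrong. The formula has no baseline term, so it does not bear on this point.

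**2. Form of the change.** HRV and the blood measures have two time points. A per-participant regression through two points is post minus pre, up to a time-scale constant. The algebra below applies to these; interoception has more than two points.

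**3. Treatment-to-mechanism path.** Variance of raw change is 2(1-rho); residual variance after baseline adjustment is 1-rho². The ratio is (1+rho)/2.

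Taking the 0.4 correlation to apply to the change score, the noncentrality is 0.4/sqrt(0.84) × sqrt(48) = 3.02. On 48 df this gives 84.2% power. Dividing by sqrt((1+rho)/2), on 47 df:

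| rho | variance ratio | adjusted power |
|---|---|---|
| 0.3 | 0.65 | 95.7% |
| 0.5 | 0.75 | 92.8% |
| 0.7 | 0.85 | 89.5% |

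**4. Mechanism-to-symptom path, autoregressive structure.** Let M1 = rho·M0 + treatment + error and Y1 = rho·Y0 + b·M1 + error, with error variance 1-rho². Within arm:

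- the covariance of the two changes is b(1-rho) + r(1-rho)²;
- the variance of mechanism change is 2(1-rho);
- so the change-only slope is b/2 + r(1-rho)/2.

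With b=0 the spurious slope is r(1-rho)/2. At r=0.4, rho=0.5 it is 0.10; with a treatment-to-mechanism effect of 0.8, the indirect effect is 0.08 instead of 0. Over r 0.2 to 0.5 and rho 0.3 to 0.9, the spurious slope runs from 0.01 to 0.175.

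With b=-0.44, r=-0.3, rho=0.5 the slope is -0.22 - 0.075 = -0.295, against a true -0.44.

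**5. False rejection of this path, b=0, N=50 (simulation).** Monte Carlo standard error at 2,500 trials is sqrt(0.05 × 0.95/2500) = 0.4 points. Where runs differed, the range is shown. The result depends on the size of r, not its sign.

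| Structure | rho | size of r | change only | + baseline mechanism | + both baselines |
|---|---|---|---|---|---|
| Autoregressive | 0.5 | 0.3 | 7.1–8.8% | 5.0% | 5.0–5.1% |
| Autoregressive | 0.5 | 0.5 | 13.0–14% | 5.1% | 4.8–5.1% |
| Autoregressive | 0.7 | 0.4 | 8.0% | 5.6% | 4.7% |
| Stable trait | 0.5 | 0.3 | 4.6–4.7% | 4.8% | 12% |
| Stable trait | 0.5 | 0.4 | 4.7–5.3% | 5.4% | 21% |
| Stable trait | 0.7 | 0.4 | 4.5% | 5.0% | 9.0% |

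Other autoregressive runs at rho=0.7 gave 5.8% to 5.9% (r=-0.3) and 7.3% (r=-0.5) for change only; at rho=0.9 and r=-0.3 the figure was 4.5%. In the stable-trait structure the baseline correlation comes only from correlated traits, with independent noise at each occasion.

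**6. Power for a true path of 0.3 (r=0.3, rho=0.5).** Autoregressive: 34% change only, 43% with baseline mechanism. Stable trait: 52% and 42%. Adding the baseline mechanism keeps the estimate at 0.30 in both, but costs power in the second.

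**The case against.** **A condensed article may omit covariates.** The sentence assigns roles and does not exclude other terms, and a fuller plan may exist. This has some weight. But the same paragraph names the baseline mechanism for the second estimator and a common baseline for the clinical mixed model, so it lists baseline terms where it uses them.

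**A baseline-adjusted estimate is already planned.** True. It would be wrong to infer that the mediation plan as a whole ignores baseline: the second estimator includes the mechanism value, and it builds on a mixed model in which baseline IBS-SSS is a modelled response. The text does not say, however, which estimate prevails if the two differ.

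**Treatment effects have their own analyses.** Also true. A reader might infer that the trial's treatment comparisons are biased or underpowered because of this omission. They are not: randomization keeps the total effect and the treatment-to-mechanism path unbiased, and both have separate mixed models. The precision loss is confined to the first mediation model.

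**The false-mediation risk could be made to look larger.** If baseline severity also raises later mechanism level (coefficient +0.2) while the baseline correlation is negative, change-only rejection reaches about 20% to 31%. That needs a lagged effect opposite in sign to the baseline correlation; with matching sign it is about 5%. Nothing in the article supports the worse case.

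**Adjusting for both baselines is not a cure.** It looks like the complete remedy, but under a stable-trait structure it creates the bias it is meant to remove (12% to 21% at rho=0.5 for r of 0.3 to 0.4). The article does not show which structure holds.

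**The analysis is exploratory.** The article does not expect significant mediation. That limits the weight of the point without removing it, because the results are meant to help choose mechanisms for a later trial.

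**Conclusion.** The point holds in a limited form. The first mediation model, as written, omits a collected baseline that its companion estimator includes.

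- The precision loss on its treatment-to-mechanism path follows for any rho below 1. It is worth about 5 to 12 points of power for rho of 0.7 down to 0.3, if the article's 0.4 correlation refers to the change score.
- The bias on the mechanism-to-symptom path is conditional. It needs correlated baselines that both regress to the mean. At rho=0.5 it raises false rejection to about 8% to 14%; at rho=0.7 the excess is small (about 6% to 8%); under a pure stable-trait structure there is none.
- The attenuation from -0.44 to about -0.30 applies if post-treatment symptoms depend on post-treatment mechanism level. It does not arise if they depend only on raw change.

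All of this rests on assumed correlations. It concerns an exploratory analysis and leaves the feasibility and acceptability outcomes untouched.

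**What to change.** In the Statistical Analysis Plan subsection, add the baseline value of the mechanism as a covariate in both equations of the first mediation model (mechanism change on treatment; clinical change on treatment and mechanism change), matching the second estimator.

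Report two sensitivity analyses: the unadjusted change-score version, and a version that also adds baseline IBS-SSS. State that adjusting for both baselines can itself bias the mechanism path under a stable-trait structure. Baseline mechanism alone is not proof against everything either: with a lagged effect of baseline severity on later mechanism, false rejection is about 10%. The spread across the three versions is therefore part of the result.

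The cost is a sentence or two of text, one residual degree of freedom per equation and two extra model fits. No new data are needed. With 20 of 50 participants enrolled as of July 2026, the change can be fixed well before analysis.

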### Study Design

This study is a single-site, parallel-group pilot RCT that aims to enroll 50 adults with IBS. Participants are randomized 1:1 to WISH 2.0 or a time- and attention-matched educational control condition. The intervention period is 9 weeks, with extended follow-up at 3 months after the intervention. The trial was prospectively registered at ClinicalTrials.gov (NCT06866106). This protocol is reported in accordance with the SPIRIT (Standard Protocol Items: Recommendations for Interventional Trials) 2025 statement (Checklist 1), the CONSORT (Consolidated Standards of Reporting Trials) 2025 statement [53], and the CONSORT extension for pilot and feasibility trials [54].

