### Assessment Visits

Participants complete 4 assessments: baseline (in-person), intervention midpoint (remote), the postintervention assessment (in-person), and the 3-month postintervention assessment (remote). Written informed consent is obtained electronically via a secure REDCap platform at the baseline visit. At each assessment, participants complete a set of self-report questionnaires electronically via a secure REDCap link. In-person assessments are conducted at the hospital’s Translational and Clinical Research Center. At the 2 in-person visits (ie, at baseline and immediately after the intervention), participants also provide a blood sample for whole transcriptome and serum inflammatory biomarker analyses and undergo HRV assessment with the emWave Pro Plus (HeartMath Institute), a validated photoplethysmography ear-clip sensor [64,65]. HRV is measured for a total of 9 minutes while participants complete a set of standardized tasks (5 min of resting at baseline, 3 min of focused attention, and 1 min of deep breathing). Additionally, participants complete a brief exit interview as part of the postintervention assessment.

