### Analytical Approach

#### Power and Sample Size

This pilot trial (N=50) is powered to evaluate feasibility and acceptability and is not designed to detect statistically significant between-group differences in exploratory clinical or mechanistic outcomes. Based on our prior proof-of-concept trial [35], with 25 participants in the PP intervention, we will have 90% power to detect a difference between our expected proportion of 80% of participants completing at least 6 (67%) of 9 PP activities and the null hypothesis (true proportion of 50% or less) at the 2-sided .05 significance level using a proportion test (power oneproportion routine in Stata version 17; StataCorp LLC). Similarly, for acceptability, assuming the same mean ratings as in our prior proof-of-concept trial [35] and an average of 6 measurements from the 25 PP intervention participants, this study has more than 90% power to detect a mean acceptability rating of ≥7.0 of 10 (simulation-based power calculation). Regarding the exploratory mediation analyses, with our sample size of 50 participants, we will have 81% power to detect a mediation effect of at least 0.44 assuming a standardized mediator with SD of 1, a standardized outcome, and a correlation between the treatment and the mediator of 0.4 at the 2-sided .05 significance level (powerMediation.VSMc command from the *powerMediation* library in R; R Foundation for Statistical Computing). Although we do not anticipate finding significant mediation effects in this pilot trial, these analyses may help identify promising candidate gut-brain mechanisms that merit examination in a future, larger randomized efficacy trial.

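### As listed, the second mediation method does not show the indirect effect: mechanism terms that are constant over visits cancel out of the time-by-treatment coefficient

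*Protocol article*

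**What the plan says.** All of this is in the Statistical Analysis Plan section of the protocol article unless another section is named.

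- The clinical model has "fixed effects for a categorical effect of time and a time-by-treatment interaction with a common baseline for the 2 groups" and an unstructured residual covariance. Its time-by-treatment terms are named as the estimate of the group difference in change, so they are the treatment effect.
- Two mediation methods follow. The first computes a change in mechanism, from a regression fitted within each participant, and a change in the clinical outcome. It then fits a mediation model to these change scores.
- The second compares the treatment effect from the clinical model with the one from "a linear mixed model including treatment, time, time-by-treatment interaction, baseline mechanistic data, and change in mechanistic data as the predictors". The plan then states: "The change will show the indirect effect through changes in candidate gut-brain mechanisms".
- No mechanism-by-time term is listed. Most mechanisms are measured only at baseline and just after the intervention (Exploratory Mechanistic Outcomes), so they yield one change per participant. The clinical questionnaires are collected at four visits (Assessment Visits).
- Power and Sample Size gives a figure for mediation: "with our sample size of 50 participants, we will have 81% power to detect a mediation effect of at least 0.44".

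**The concern.** The second method looks for mediation in how far the time-by-treatment coefficient moves when the mechanism is added. A covariate that takes the same value at every visit, baseline included, raises or lowers a participant's whole profile by a constant. It can explain differences in level between participants but not differences in change, and the treatment effect here is a difference in change. So the coefficient has no reason to move, even for a mechanism that carries the whole effect.

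The two models also treat baseline differently. The clinical model forces a common baseline mean, while the mechanism model lists a treatment main effect and so lets the baseline means differ. That alone makes the two coefficients differ in any one trial, and the plan would read this difference as an indirect effect.

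At stake is the interpretation of Aim 2. The second method gives the same answer for a true mediator as for no mediator, so it would seem to contradict the change-score model when that model is right.

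**Working it through.** **The plan's own figure.** Inputs: N = 50, effect 0.44, "a correlation between the treatment and the mediator of 0.4 at the 2-sided .05 significance level", and "assuming a standardized mediator with SD of 1, a standardized outcome". Taking 0.44 as the mediator's coefficient b and the residual SD as 1:

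power = Φ(b·SD·√(N(1−ρ²)) − 1.96) = Φ(0.44·√(50·0.84) − 1.96) = Φ(2.852 − 1.96) = Φ(0.892) ≈ 0.81.

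The 81% is reproduced. It comes from a formula for a regression with a single outcome, so it says nothing about the second method.

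**Algebra.** Let A be treatment, M₀ the baseline mechanism, D the mechanism change, t the visit (0 = baseline) and Ȳ the observed means. The mechanism model as listed is

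Y(i,t) = α(t) + θA(i) + δ(t)A(i) + γ₀M₀(i) + γ₁D(i) + e(i,t), with δ(0) = 0.

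1. Treatment, time and their interaction give each arm a free mean at each visit. For any γ and any covariance matrix, the likelihood equations with complete data give the fitted mean for arm g at visit t as Ȳ(g,t) − γ₀M̄₀(g) − γ₁D̄(g).
2. The part subtracted is the same at every visit. So δ̂(t) = [Ȳ(1,t) − Ȳ(1,0)] − [Ȳ(0,t) − Ȳ(0,0)], the raw difference in mean change. Neither γ appears in it. In simulated fits the two agreed to about 1e-14.
3. With complete data, the clinical model with its common baseline gives the baseline-adjusted difference, [Ȳ(1,t) − Ȳ(0,t)] − β̂·[Ȳ(1,0) − Ȳ(0,0)], where β̂ is the slope of the visit-t outcome on the baseline outcome.
4. Subtracting step 2 from step 3 gives (1 − β̂)·[Ȳ(1,0) − Ȳ(0,0)]. This is what the plan calls the indirect effect. It contains only the chance baseline difference between arms, which randomization centres on zero.

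**Simulation.** "Participants are randomized 1:1 to WISH 2.0 or a time- and attention-matched educational control condition", so 25 per arm, with four visits. A correlation of 0.4 with a 0/1 treatment indicator (SD 0.5) and mediator SD 1 means a = 0.4/0.5 = 0.8. The true indirect effect is 0.8·b: 0 for b = 0, 0.352 for b = 0.44 and 0.80 for b = 1. Assumed: residuals made of a participant effect plus independent noise, and half of the effect present at midpoint. There were 100 replicates per setting (60 with dropout). Entries are the mean difference between models at the postintervention visit.

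| Mechanism model | True 0 | True 0.352 | True 0.80 |
|---|---|---|---|
| As listed | 0.016 | 0.016 | 0.017 |
| As listed, 20% dropout (assumed) | not run | 0.002 | 0.003 |
| As listed, compound symmetry | not run | 0.011 | 0.012 |
| Treatment main effect dropped | 0.000 | 0.096 | 0.292 |
| Main effect plus interaction taken as the effect | −0.022 | 0.211 | 0.508 |
| Mechanism-by-time terms added | 0.016 | 0.380 | 0.843 |
| Change coded 0 at baseline, time-varying | 0.025 | 0.389 | 0.852 |

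The Monte Carlo standard error in the first row is about 0.012, so those three means are indistinguishable from zero and from each other. The SD across single trials is about 0.12, which is the baseline noise of step 4. When the clinical model is also given a treatment main effect, the difference is 0.000 in every complete-data replicate.

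Dropping the treatment main effect recovers 0.096/0.352 = 27% and 0.292/0.80 = 36%. Taking the main effect plus the interaction recovers 60% and 64%. A separate simulation with a fully mediated effect of 0.48 gave −0.002 for the model as listed, 0.14 (30%) with a common baseline and no treatment main effect, and 0.47 with mechanism-by-time terms.

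**The case against.** The strongest objection is that the result depends on how the change term is coded by visit, and the sentence describing the second model does not say. The within-participant regression is introduced for the change-score model. In a long-format data set an analyst could set change to 0 at baseline, and the interoception questionnaire (MAIA-2), measured at all four visits, allows a visit-specific change. With such coding the same list of predictors does detect mediation: 0.389 of 0.352 and 0.852 of 0.80 in the table, and 0.41 of 0.48 in another run. This stands as a limit on the claim. It does not remove it, because the only definition of mechanism change in the text gives one number per participant, and heart rate variability, RNA and serum markers have just two measurements.

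A second objection is that an article condenses the plan and may leave out interaction terms. But the article lists the predictors and asserts what the comparison shows, and for the listed model that assertion is wrong.

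Third, a reader might infer that the trial cannot study mediation, or that promising mechanisms would be discarded. The document does not support either. The change-score mediation model does not have this defect, and no rule drops a mechanism on the strength of the second method. The plan also says that significant mediation is not expected in this pilot.

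**Conclusion.** Wrong as written, with moderate severity. With one mechanism-change value per participant entered as a main effect, the second method returns baseline-imbalance noise around zero (SD about 0.12 in the simulated standardized units) whether the true indirect effect is 0, 0.352 or 0.80. A larger sample would shrink the noise but would not make the method respond to mediation.

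The exact identity rests on complete data, the listed treatment main effect and the interaction as the treatment effect. The simulations suggest that 20% dropout changes little. The estimate in a single trial is not exactly zero, and the conclusion does not hold if change is coded 0 at baseline or interacted with time. The primary outcomes of feasibility and acceptability are untouched, and the change-score model still addresses Aim 2. The practical harm is a second result that appears to contradict that model when a mechanism truly mediates.

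**What to change.** Use the same common-baseline structure, without a treatment main effect, in both models. In the second, interact baseline mechanism and mechanism change each with categorical time. Define the indirect effect as the change in the postintervention time-by-treatment coefficient, with a bootstrap confidence interval that resamples participants and refits both models.

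A close alternative is to enter mechanism change as a time-varying covariate equal to 0 at baseline, with its value at each later visit stated. If neither is wanted, delete the second method and rely on the change-score mediation model.

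The cost is a few words in the analysis section and no new data. With 20 participants enrolled as of July 2026 and completion expected in August 2028, there is time to make the change before the final analysis.
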